## Abstract

**Background:**

The purpose of the present study is to introduce an adapted protocol of *in vivo* exposure for fear avoidant back pain patients and its implementation in the German health care system without multidisciplinary teams. Case studies demonstrated promising effects but three preceding randomized controlled trials (RCTs) could not support the former results. More empirical support is necessary to further substantiate the effectiveness of *in vivo* exposure.

**Methods:**

A total of 108 chronic low back pain patients are randomly assigned to one out of three conditions (A: exposure_long (15 sessions), B: exposure_short (10 sessions) or C: control condition cognitive behavioral therapy (15 sessions)). The inclusion criteria are: back pain ≥3 months and a sufficient level of fear-avoidance. An effect evaluation, a process evaluation and an economic evaluation are conducted. Primary outcomes are pain-related disability and pain intensity. Secondary outcomes are: emotional distress, fear avoidance, catastrophizing and costs. Data are collected at baseline, upon completion of the intervention, after 10 sessions, and at six months following completion of treatment. Besides the comparison of exposure *in vivo* and cognitive behavioral therapy (CBT), we additionally compare a short and a long version of exposure to analyze dose response effects.

**Discussion:**

This is, to our knowledge, the first RCT comparing *in vivo* exposure to psychological treatment as usual in terms of cognitive behavioral therapy. Results will help to find out whether a tailored treatment for fear avoidant back pain patients is more effective than a general pain management treatment.

**Trial registration:**

The trial has been registered to ClinicalTrial.gov. The trial registration number is NCT01484418

## Background

Chronic low back pain (CLBP) is one of the most common health problems in Western societies. In Europe, one out of every five people experiences significant back pain that infers with quality of life [1]. In addition to its broad prevalence, CLBP is one of the major causes of medical expenses, work absenteeism and disability [2]. Since cognitive behavioral models of CLBP have become more widely accepted, a large variety of behavioral interventions have become available for the treatment of CLBP [3]. Psychological interventions have been found to be effective, with cognitive behavioral treatments showing moderate to large effect sizes for reducing self-reported pain, pain-related interference, depression and disability [4]. However, it is unknown which interventions work best for particular subgroups of patients [3,5,6] and more research is needed to define subgroups [5]. Vlaeyen and colleagues developed a treatment focusing on fear-avoidant back pain patients [7]. This treatment, known as graded *in vivo* exposure, is based on the fear-avoidance model of chronic pain, which postulates that fear and avoidance of movement contributes to the maintenance of pain via mechanisms of classical conditioning and reinforces disability [8]. As in the treatment of anxiety disorders, the patient is gradually exposed to a feared stimulus, which in the case of CLBP is movement believed to lead to pain or potential injuries to the back. Approximately 10 years ago, the first single case designs showed that *in vivo* exposure reduced pain disability, pain catastrophizing, and pain-related fears with large effect sizes [7,9-11]. In addition to the case studies, three randomized controlled trials (RCTs) have compared graded exposure to a waiting list, graded activity programs [12,13] or treatment as usual, for example, usual medical care [14]. These studies found that *in vivo* exposure was superior to control conditions at reducing pain-related fears and catastrophizing. Only one study found effects (at the trend level) on pain-related disability [14]. In summary, the efficacy of exposure treatment in the RCTs was inferior relative to the preceding case studies.

Therefore, as emphasized by the authors of previously published systematic reviews, additional RCTs, including larger sample sizes, cost-effectiveness-analyses, mediational analyses and treatment fidelity assessments, are required [15-17].

### Problem definition

Several questions concerning exposure *in vivo* treatment (EXP) for chronic back pain remain unanswered:

First, there is a lack of empirical evidence regarding whether interventions tailored for particular subgroups, such as *in vivo* exposure for fear-avoidant pain patients, are more effective than traditional cognitive behavioral treatments for the management of chronic pain problems (CBT-P). Although a variety of definitions of CBT exist, we favor the description provided by Turk, which incorporates behavioral (principles of learning), emotional and cognitive factors. Thus, we attempt to teach our patients “to recognize the connections linking cognitions, affective, behavioral, and physiologic responses together with their joint consequences” [18]. Thus far, *in vivo* exposure has not been compared to cognitive behavioral treatment as it is usually delivered in clinical practice.

Second, it is unknown how many sessions of EXP are needed to achieve sufficient results and that patients get the needed benefit. In a single case paradigm, Vlaeyen *et al*. found significant reductions in disability and pain-related fears after only three exposure sessions [7]. On the other hand, recent reviews indicate that there is evidence that prolonged psychological treatment in chronic pain patients is beneficial [19,20]. Hansen and colleagues showed that between 13 and 18 sessions of therapy in general are required for 50% of patients to improve [21]. Besides the research on the dose–response relationship in psychotherapy in general it is also very important to evaluate and develop the adequate treatment of more specialized treatment approaches. Thus, the analysis of the dose–response relationship in exposure treatment for chronic pain is needed to establish an effective and economical length of treatment.

Third, CLBP is often described as a socio-economic problem because it is a major cause of medical expenses, work absenteeism and disability [2]. However, economic aspects of CLBP treatments (for example, cost-effectiveness) have generally received little attention and thus should be incorporated into RCTs [5,22].

### Objectives

The present investigation, which began recruitment in August 2011 and is currently ongoing, utilizes a three-arm randomized controlled trial method to assess the efficacy of graded *in vivo* exposure (EXP) for CLBP relative to cognitive behavioral therapy (CBT-P). To our knowledge, this is the first study to implement *in vivo* exposure for CLBP patients in an outpatient setting in Germany, and is also the first study to compare graded *in vivo* exposure to CBT. Accordingly, we will assess the feasibility of this new treatment approach. Dose-effects will be analyzed by comparing a short and a long version of EXP. In addition, cost-effectiveness will be evaluated. Besides, the main questions meditational analyses and examination of effects of generalization are planned.

#### Research questions

1) Is EXP more effective (at post-treatment and at six-month follow-up) at reducing pain-related disability and pain intensity (primary outcomes) as well as other symptoms compared to CBT-P in patients with fear-avoidance beliefs?

2) Are there any differences in treatment effects between the short (10 sessions) and the long (15 sessions) versions of exposure at post-treatment and at six-month follow-up?

3) What is the cost-effectiveness of EXP as compared to CBT-P?

## Methods

### Design

A three-arm randomized controlled clinical trial will be performed in a university-based outpatient clinic in Marburg (Psychotherapieambulanz der Universität Marburg, PAM), Germany.

Patients are assigned to one of three conditions (A: exposure_long; B: exposure_short or C: control condition, specifically cognitive behavioral therapy for the management of chronic pain).

The study includes assessments at baseline, mid-treatment, post-treatment and six-month follow-up, as well as process measures.

The study was approved by the ethics committee of The German Association of Psychology (DGPS, WR 052010_1).

### Participants

Our target sample is 108 patients with CLBP. Potential study patients will be recruited via advertisements in local newspapers, doctors´ offices and from the waiting list of our outpatient clinic. Potential participants are screened through an initial phone interview with a research assistant examining the basic inclusion criteria. Those who fulfill all of the basic criteria are invited to a second screening in our outpatient clinic where the criteria of fear-avoidance and disability are assessed.

### Inclusion and exclusion criteria

Patients with CLBP are included if they meet all of the following criteria:

1. Basic criteria:

1.1 Chronic low back pain for at least three months.

1.1 Age: 18 to 66.

2. Additional criteria:

2.1 TSK (Tampa Scale of Kinesiophobia) [23] ≥35 or Phoda-Profile (Photo Series of Daily Activities) [24]: harm ratings of 13 activities >50, including 8 >80 (range 0 to 100, with 0 = “not harmful at all” and 100 = “extremely harmful for my back”).

2.1 Sufficient level of disability, as defined by QBPDS ≥15 (Quebec Back Pain Disability Scale) [25].

Exclusion criteria include: back surgeries during the last six months or planned surgeries, Red Flags [26], inability to read or write in German, pregnancy, alcohol addiction, psychotic disorders and current psychological treatment. Patients are excluded if they are unable to attend sessions regularly for physical or psychological reasons.

Physical and psychological comorbidities, such as depression, are not exclusionary so long as patients are able to attend sessions and complete homework. Recruitment started in August 2011 and will continue until the target sample of 108 patients with CLBP is achieved (expected to occur near the end of 2013). We anticipate that this timeframe will be adequate to achieve recruitment goals.

### Sample size calculation

To identify the target number of participants we used the G-Power Analysis software program (University of Düsseldorf, Germany http://www.psycho.uni-duesseldorf.de/abteilungen/aap/gpower3.) [27]. Based on the effects of previous RCTs, we expected a small effect group x time (repeated measures) of 0.2 for the comparison of three groups (assuming an alpha level = 0.05, two-tailed, β = 0.95, correlation between measurements = 0.5). Results of the power analysis indicated a required sample size of 36 participants per group, for a total of 108. The data will be analyzed with the intent-to-treat (ITT) approach using the last value carried forward and including all patients who intended to participate, regardless of whether they dropped out or not.

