### Patient allocation and randomization

Patients are randomized to one of three conditions following a predetermined and computer-generated randomization schedule, pre-stratified by degree of pain catastrophizing (PCS) [28] and disability (PDI) [29]. The median scores of the pain catastrophizing and disability data from a previous study are used as cutoffs. Within each stratum, a randomized block design with a block size of nine is used to ensure equal distribution of important patient characteristics. The randomization procedure is performed by a blinded research assistant who prepares sequentially numbered, sealed, opaque envelops. As is common in psychological treatments, it was not feasible to blind patients or therapists to treatment condition.

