### Data collection

Data are collected at baseline (T0), after 10 sessions (T1, completion of EXP short), upon completion of the intervention (T2), and six months following completion of treatment (T3). Thus, participants in the short version of EXP complete only three assessments. Questionnaires are completed at home via the internet. This procedure reduces missing data and helps to keep study therapists blind to outcome data. Supplemental evaluations are carried out weekly, including process variables. If patients do not have internet access the assessment are provided on a computer in our outpatient clinic. Video recordings are carried out during each session to gather objective data for later analysis of treatment fidelity.

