### Data analysis

The latest version of The Statistical Package for Social Science (IBM SPSS Statistics) version 19is used for data analyses. Intention-to-treat analyses (ITT) used to account for deviations from random allocation and missing data. A repeated measures design will be used with primary and secondary measures as dependent variables, group as the between-subjects factor, and time of measurement as the within-subjects factor.

Possible confounding variables (for example, duration of complaints) will be considered and included as covariates according to the results of correlation analyses. Effect sizes (Cohen´s d) will be calculated to determine the magnitude of the mean differences between groups on the outcome variables. According to Cohen´s guidelines, an effect size of .2 indicates a small effect, .5 a medium effect and .8 a large effect [52]. We consider a 30% reduction on the NRS to indicate clinically important change on the core outcome measure of pain intensity [53]. The economic evaluation consisted of a cost-utility analysis and a cost-effectiveness analysis. For both analyses, the incremental cost-effectiveness ratio (ICER) was calculated as (C1-C0)/(E1-E0) where C is the cost and E is the effect and the experimental and comparator conditions are indexed with the 1, 0 subscripts.

The incremental cost-utility ratio will focus on the net costs per quality adjusted life years (QALY) gained. The cost-effectiveness ratio focuses on the net costs per reliable and clinically improved case of disability/pain. Probit analysis will be used for dose–response effects. This approach based on probability theory and includes determining the observed rates and resulting probability of a response for a particular treatment.

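### The claimed 95% power for a "small" effect of 0.2 most likely refers to Cohen's f, which here means a difference between arms of about 0.85 SD or more; power for a truly small d = 0.2 is about 10–13%

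*Protocol article*

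**What the plan says.** The section Sample size calculation (protocol article) reports that "we used the G-Power Analysis software program" and that "we expected a small effect group x time (repeated measures) of 0.2 for the comparison of three groups". The other inputs are given as "assuming an alpha level = 0.05, two-tailed, β = 0.95, correlation between measurements = 0.5". The outcome is "Results of the power analysis indicated a required sample size of 36 participants per group, for a total of 108". The section names neither the metric of the 0.2 nor the number of measurements entered.

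The section Data analysis plans a repeated-measures analysis with group as between-subjects and time as within-subjects factor. It expresses group differences as Cohen's d, for which "an effect size of .2 indicates a small effect, .5 a medium effect and .8 a large effect".

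The section Data collection lists four assessment points, but "Thus, participants in the short version of EXP complete only three assessments". The number of measurements behind the calculation therefore cannot be read off from the schedule.

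**The concern.** The article calls 0.2 small and later defines small as d = 0.2. A reader will naturally conclude that 36 patients per arm give 95% power to detect a 0.2 SD difference between arms. No three-arm trial of this size does that with a correlation of 0.5 between measurements. Either 0.2 is on another scale, and the adjective misleads, or the power is far below the stated value.

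What is at stake is how a non-significant result can be read. The comparator is an active treatment, and the Conclusions section asks whether a specialised treatment is needed or whether standard CBT is enough. If the trial is believed to have 95% power for small differences, a null result looks much more informative than it is. The section also says the expected effect rests on earlier RCTs, while the Background reports that only one of these found an effect on disability, at trend level. A very large difference against active CBT is hard to square with that account.

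**Working it through.** **Inputs.** From Sample size calculation: α = 0.05, power 0.95 (printed as β), correlation ρ = 0.5, effect 0.2, k = 3 groups, N = 108. From Data analysis: group × time interaction. Not stated, so taken in turn: m = 2, 3 or 4 measurements. Sphericity is assumed (ε = 1).

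**Step 1: reproduce the article's figure.** G*Power's default for a within-between interaction uses a non-central F with λ = f²·N·m/(1−ρ), df1 = (k−1)(m−1) and df2 = (N−k)(m−1). For f = 0.2, m = 2, N = 108: λ = 0.04 × 108 × 2/0.5 = 17.28, df = 2 and 105, power = 96.5%.

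| m | N for 95% power, equal groups | Power at N = 108 |
|---|---|---|
| 2 | 102 | 96.5% |
| 3 | 81 | 99.0% |
| 4 | 69 | 99.8% |

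With G*Power's alternative effect-size option (as in Cohen), f = 0.2 would need 393, 240 or 180 patients for m = 2, 3, 4. Reading 0.2 as d needs well over a thousand (step 3). Only the default f comes near 108, most closely with m = 2.

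**Step 2: translate f = 0.2 into a difference in SD.** Let the effect be fully present from the first post-baseline assessment, and let d be the largest between-arm difference in change, in SD units of a single measurement. (With ρ = 0.5 the variance of a change score is 2(1−0.5) = 1, so the SD of change is the same.) The interaction f per unit of d is SD(arm pattern) × √(m−1)/m. The SD of the arm pattern is 0.4714 if both exposure arms differ equally from CBT-P (1, 1, 0) and 0.4082 if the arms are evenly spaced (1, ½, 0).

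For m = 2, two arms versus one: 0.4714 × 0.5 = 0.2357, so d = 0.2/0.2357 = 0.85.

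| m | d at f = 0.2, two v one | d at f = 0.2, evenly spaced |
|---|---|---|
| 2 | 0.85 | 0.98 |
| 3 | 0.90 | 1.04 |
| 4 | 0.98 | 1.13 |

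All exceed 0.8, the article's threshold for large. If the effect builds up more slowly over time, the implied difference rises to as much as about 1.3 SD.

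**Step 3: power at N = 108 for effects on the d scale.** Convert d to f as in step 2 and apply step 1.

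| m | d = 0.2, two v one | d = 0.2, evenly spaced | d = 0.5, two v one | d = 0.5, evenly spaced |
|---|---|---|---|---|
| 2 | 12.7% | 10.7% | 57.1% | 44.9% |
| 3 | 12.1% | 10.2% | 59.4% | 46.0% |
| 4 | 11.4% | 9.6% | 57.9% | 44.3% |

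Omnibus power of 95% at d = 0.2 would take about 1,570 to 1,740 patients (two v one) or about 2,090 to 2,320 (evenly spaced).

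**Step 4: what 108 patients can detect for the research questions.** For a change-type comparison with variance 1, the difference detectable with 80% power is (1.96 + 0.84) × √(1/n1 + 1/n2).

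- Pooled exposure v CBT-P (72 v 36): 2.80 × √(1/72 + 1/36) = 2.80 × 0.204 = 0.57 SD.
- Long v short exposure (36 v 36): 2.80 × √(2/36) = 2.80 × 0.236 = 0.66 SD.

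The non-central t gives values about 0.01 higher. Baseline adjustment at ρ = 0.5 reduces the variance to 1 − 0.25 = 0.75, multiplying these by 0.866: 0.50 and 0.57 SD. All are before dropout.

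**The case against.** The strongest reply is that nothing was miscalculated. For f = 0.2 with two measurements, 108 patients give 96.5% power, so the software was used soundly and only the label is at fault. That stands: this is an unnamed metric and a misleading adjective, not a failed power calculation. It is also true that the f reading is inferred, since the article never states it.

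Several stronger readings are tempting, but the documents do not support them.

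- A reader might infer that the inputs fail to return 108. The number of measurements is not stated, so there is no complete input set to fail. With m = 2 the answer, 102, rounds up to 108 in multiples of nine, and the randomisation section says "a randomized block design with a block size of nine is used".
- A reader might infer that nothing was allowed for dropout. None is mentioned, but 108 exceeds every default-f requirement above, and 81/(1−0.25) is exactly 108. The article cannot settle this.
- A reader might infer that the investigators will take a null result as proof that CBT is adequate. The Conclusions section only poses this as an open question.
- The printed β = 0.95, taken literally, would mean 5% power. It is plainly a slip for 1−β.

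What the reply does not remove is that the article attaches 95% power to an effect it calls small, and its own definition of small does not fit that effect.

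**Conclusion.** The point holds as a misstatement of what the design can detect. Ninety-five per cent power for a small effect, on the scale the article itself defines, is not a property of this trial. The effect actually powered for is most likely f = 0.2, a between-arm difference in change of roughly 0.85 to 1.13 SD. For a medium difference of d = 0.5 the chance of a significant omnibus interaction is near one half.

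These figures rest on ρ = 0.5 and equal arms of 36, as stated, and on sphericity, an effect fully present from the first post-baseline assessment, two to four measurements and no loss to follow-up, all of which are assumed. The ranges cover both patterns of arm means; slower onset of effect would lower the power further.

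**What to change.** Keep N = 108 and rewrite the justification:

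- delete the word small;
- write power (1−β) = 0.95;
- state that 0.2 is Cohen's f for the group × time interaction (if the investigators confirm this) and give the number of measurements entered;
- give its equivalent as a between-arm difference in change, in SD, for that number of measurements and a stated pattern of arm means;
- add the differences detectable with 80% power under the planned change-type analysis (ρ = 0.5, before dropout): about 0.57 SD for pooled exposure versus CBT-P (72 v 36) and about 0.66 SD for long versus short exposure (36 v 36).

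The smaller values of 0.50 and 0.57 SD should be quoted only if a baseline-adjusted analysis is also specified; the Data analysis section currently plans a repeated-measures group × time model.

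The cost is wording only: no extra patients and no change to data collection. The stated sensitivity of the trial becomes less favourable, and it should be corrected before results are interpreted.

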### Process evaluation

Participants complete a short survey online each week to measure mediating variables relevant to the process of change. The battery includes the TSK, PDI, IPAQ, QBPDS, a numeric rating scale assessing pain severity, and an 11-item scale assessing coping with pain, self-efficacy and avoidance rated on an 11-point scale.

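### Last value carried forward is fixed as the only missing-data method; it can bias the arm comparisons, including short v long exposure at equal dropout

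*Protocol article*

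**What the plan says.** The missing-data rule stands in the Sample size calculation section: "The data will be analyzed with the intent-to-treat (ITT) approach using the last value carried forward", "including all patients who intended to participate, regardless of whether they dropped out or not".

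The Data analysis section does not mention carrying values forward, but it again gives intention-to-treat the task of handling incomplete data: "Intention-to-treat analyses (ITT) used to account for deviations from random allocation and missing data". The model is a repeated-measures design with "group as the between-subjects factor, and time of measurement as the within-subjects factor". No likelihood-based model, multiple imputation or sensitivity analysis is named in either place.

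The Data collection section sets four assessments: baseline (T0), after 10 sessions (T1), completion (T2) and six months after completion (T3). For the 10-session exposure arm, T1 is completion, so "participants in the short version of EXP complete only three assessments". Separately, under Process evaluation, "Participants complete a short survey online each week to measure mediating variables"; that battery includes the PDI and the QBPDS, the two primary disability measures.

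**The concern.** Intention-to-treat means analysing everyone in the arm to which they were randomised. It does not require a missing outcome to be filled with an old one. Last value carried forward adds the assumption that nothing changes after the last assessment, and that assumption is hard to defend here for three reasons.

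- All three arms are active treatments meant to reduce disability. Carrying T0 forward scores a patient lost in treatment as having no change at all.
- A patient lost after T2 has the post-treatment value carried to T3. That assumes neither relapse nor further gain over six months, yet the six-month result is part of research questions 1 and 2.
- The value available to carry depends on the arm. In EXP_short, baseline is the only scheduled assessment before completion. In EXP_long and CBT-P, a late dropout can be carried from T1.

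Dropout may also differ by arm, because the arms differ in length (15, 10 and 15 sessions) and only exposure confronts feared movements. The article foresees dropout (it has a standardised dropout evaluation) but gives no rate. At stake is the primary group-by-time comparison, and most directly the short v long question.

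**Working it through.** The article has no figure of its own on this point to reproduce, so the check shows the mechanism under stated assumptions.

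**Inputs from the article:** 36 patients per arm; correlation between measurements 0.5; assessment schedule as above.

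**Assumed, not in the article:**
- outcome SD of 1 and a true gain of 0.8 SD by T2 in each arm, with two thirds of it reached by T1;
- dropout completely at random, with dropouts sharing the arm's mean trajectory after they leave;
- in a 15-session arm, 60% of dropouts leave before T1 (carry baseline) and 40% between T1 and T2 (carry T1).

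**Step 1. Gain lost per dropout.** Carried from baseline, 0.8 SD is lost. Carried from T1, 0.8 × 1/3 = 0.267 SD is lost. Average: 0.6 × 0.8 + 0.4 × 0.267 = 0.587 SD.

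**Step 2. False difference between two 15-session arms with no true difference** = 0.587 × (difference in dropout proportion).
- 30% v 10%: 0.587 × 0.20 = 0.117 SD.
- 25% v 10%: 0.587 × 0.15 = 0.088 SD.
- 20% v 20%: 0.

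**Step 3. Type I error.** The standard error of the difference in change with full data is √(2 × 2(1 − 0.5)/36) = 0.236; with carried values the simulated model standard error is about 0.228. The bias is then 0.117/0.228 = 0.51 standard errors. The two-sided 5% test rejects with probability Φ(−1.96 + 0.51) + Φ(−1.96 − 0.51) ≈ 8%. For 25% v 10%, 0.088/0.229 = 0.38 and the result is about 6.7%. Simulation of 40,000 trials per scenario gives 7.9% and 6.8%, and 5.0% at 20% v 20%.

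**Step 4. True difference of 0.40 SD, 20% dropout in both arms.** The fraction of effect lost per dropout is 0.6 + 0.4 × 1/3 = 0.733. Expected estimate: 0.40 × (1 − 0.20 × 0.733) = 0.341 SD. Simulation gives 0.34.

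**Step 5. Short v long exposure, 20% in-treatment dropout in both, no true difference.** EXP_short dropouts can carry only baseline: 0.20 × 0.8 = 0.160 SD lost. EXP_long: 0.20 × 0.587 = 0.117 SD lost. False difference: 0.160 − 0.117 = 0.043 SD in favour of the long version, although dropout is equal.

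**Step 6. Standard errors.** At 30% v 10% the mean model standard error and the empirical spread of the estimate are both 0.228; at 20% v 20% both are 0.229. The excess rejections in Step 3 therefore come from bias.

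**Range.** With three arms and 30–40% dropout in two arms v 10% in the third, the false difference runs from about 0.05 SD (all carried from T1; type I error 5.3–6.1%) to 0.24 SD (40% v 10%, all carried from baseline; type I error 19.7%).

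**The case against.** Several points on the other side are fair.

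- **The size depends on rates that the article does not give.** This stands. A bias of 0.09–0.12 SD needs a 15–20 point imbalance in dropout and is about half of one standard error. With equal dropout and no true effect, two arms of the same length show no bias, and shrinkage of a real effect is conservative for a superiority question.
- **Dropouts may truly stay at their last level.** The calculation lets them share the arm's later gain. If they did not, carrying forward would be closer to the truth and a mixed model could be the biased method. The article supports neither version. That is a reason not to rest the primary analysis on the no-change assumption alone.
- **Stopping treatment is not the same as a missing outcome.** Questionnaires are completed online at home, so some who stop may still report. This lowers the amount carried forward but does not change the rule.
- **The weekly scores might be what is carried.** The article does not say which last value is used, so this cannot be excluded. Nor does it say that the weekly surveys continue to T3, or that the weekly pain rating is one of the primary pain measures.

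A reader might also infer that last value carried forward makes the standard errors too small and the intervals too narrow. That is not shown. Carried values do count as observed, and the standard error of 0.22–0.24 is below the 0.265 of a complete-case analysis at 30% v 10%. But the model standard error matches the estimator's actual spread, and type I error is about 5% when dropout is equal. Nor do the figures demonstrate bias under outcome-dependent (missing-at-random) dropout, because the simulated dropout was completely at random.

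**Conclusion.** The concern holds in this form: the article names one missing-data method, and that method biases the comparison when dropout differs by arm or when change continues after the last value. The short v long comparison is exposed even at equal dropout, because EXP_short has no mid-treatment assessment to carry. This is a choice that the article makes, not a detail left to an analysis plan.

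Under the assumptions listed, the false difference is about 0.09–0.12 SD for 25–30% v 10% dropout, roughly half of what the article calls a small effect (0.2), with two-arm type I error of about 7–8%. A true 0.40 SD is estimated as about 0.34 SD with 20% dropout in both arms. The short v long bias at 20% dropout in both is about 0.04 SD. The actual size and direction cannot be determined from the article.

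**What to change.** In the Sample size calculation and Data analysis sections, replace last value carried forward as the primary method by one of these:

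1. a likelihood-based mixed model for repeated measures, including all randomised patients in their allocated arm with every outcome they provide and no single imputation. SPSS, the software already named, offers this as MIXED, and the model accepts the assessment that EXP_short does not have; or
2. multiple imputation, with the weekly PDI and QBPDS scores as auxiliary data.

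Keep last value carried forward only as a sensitivity analysis, and say which last value (scheduled or weekly) is carried.

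The cost is a change of analysis wording, with no new data. By May 2013, 71 of the 108 patients had been randomised and recruitment was continuing, so the change could be made before analysis. The small downside is that the primary result then rests on a missing-at-random assumption, which should be stated.
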